#### Interim analyses

No interim analyses will be performed as the primary outcome measure will only be available once the trial is complete. The intervention is behavioural and focused on healthcare professionals; consequently, it was believed not to be necessary to access the primary outcome data, relating to rehospitalisation, until the trial was completed.

#### Additional analyses

A sensitivity analysis will adjust for relevant baseline characteristics, that is, age and the number of pre-admission medicines.

The number of medications stopped during the enhanced data collection period will be compared between the control and intervention using a linear mixed model including hospital as a random effect, and fixed factors will include randomisation arm and time period.

The proportion of patients per arm where a pre-admission medicine is proactively deprescribed will be compared using logistic regression, the same model as above.

The QoL measures will be compared between the control and intervention using a linear mixed model including hospital as a random effect, and fixed factors will include randomisation arm and time period.

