### Outcomes

Selection of outcome measures was based on a previously developed core outcome set designed for hospital-based deprescribing interventions.^17^ The primary outcome measure was selected as hospital readmission within 90 days as this was considered to be sufficiently sensitive and proximal to the intervention.

Outcome data are summarised in table 1. Costs and resource use, as well as economic outcomes, will be captured via expert opinion and review of study records where relevant.

**Table 1 T1:** Outcome data

Routinely collected data (without consent)	When	How
Mortality for any reason	90 data post-discharge	Hospital records and NHS England* Office of National Statistics Mortality records
Number of hospital stays†	90 data post-discharge	Hospital records and NHS England* Hospital Episode Statistics Admitted patient care
Number of planned and unplanned admissions and readmissions for treatment or monitoring of health†		

Intensive data collection (with consent)¶	When	How
Satisfaction with deprescribing process‡	2 weeks post-discharge	Postal questionnaire
Adverse drug events§	90 days post-discharge	Telephone questionnaire
Health-related quality of life (EQ-5D-5L††)^23^	Pre-discharge 90 days post-discharge	Face to face on ward Telephone questionnaire
Primary care consultations†	90 days post-discharge	Telephone questionnaire
Community pharmacy dispensed medicines†	90 days post-discharge	NHS England*
Number of ‘Regularly’ prescribed medicines	On admission and discharge	Routine hospital records^**^
Number of ‘As required’ prescribed medicines		
Number of medicines prescribed on admission which are stopped during admission while on study ward		
Number of medicines prescribed on admission with dosage reduced during admission while on study ward		
Number of stopped medicines prescribed on admission which are stopped during admission while on study ward and then restarted		

* National agency responsible for collation and provision of healthcare data.

† Captured for additional health economic analysis purposes.

‡ Questionnaire with 12 items based on previously published survey tool.^25^

§ Questionnaire with 17 items inviting respondents to indicate whether or not they have experienced any of the medication-related adverse events listed. The list is derived from an observational study of medication-related adverse events.^26^

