¶ During enhanced data collection periods, consent/assent for routine data collection was sought wherever possible, but where not possible, Section 251 approval was applied. Where participants declined to consent/assent, routine data was not collected.

** To enable the outcomes regarding medication to be collated the following data will be collected: Name, dose and frequency of all medicines prescribed to the patient before any changes were made during the hospital admission. Any changes made to the above medicines (stopped, dose reduction, dose increase or change in frequency). Name, dose and frequency of any new medicines started during the admission that are requested to be continued post discharge.

†† EQ-5D-5L, EuroQol 5-Dimension 5-Level.

NHS, National Health Service.

Geriatrician and pharmacist participants will complete the following at the point of site set up:

Short demographics questionnaire (age, gender, ethnicity, job role, grade, training).Mechanism of action questionnaire—an 11-item questionnaire measuring the extent to which the CHARMER intervention has addressed the intended four barriers and one enabler to proactive deprescribing.^15^Process of deprescribing questionnaire—a 19-item questionnaire capturing the extent to which practitioners undertake the steps within the process of proactively deprescribing in hospital.^18^

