### Sample size

The underpinning feasibility study showed that recruitment to an original planned cluster randomised trial would require recruitment of over 40 hospitals and was unlikely to be achieved. Consequently, the design was changed to a stepped wedge due to the increased power provided by this design.

With a baseline step with all hospitals receiving the control followed by four separate steps, each randomising five hospitals to switch from control to intervention (20 hospitals in total) will have 89.5% power to detect a difference of 16.7% to 13.7% of 90-day re-admission rates assuming a 5% level of significance and an intra-class correlation coefficient (ICC) of 0.05 and 200 participants per hospital per step. The total sample size will be 20 000 participants. The anticipated 3% difference is similar, but slightly smaller, to the difference reported in the MedSafer study.^19^

From our feasibility study findings, we estimate that 10% of patients on study wards or consultees will provide written (or, if required, virtual) informed consent for additional patient-reported outcome data. For the enhanced data collection period, where medication changes are recorded in hospital, then if the sites collect data on 60 participants in each of the enhanced data collection periods, the study will have 99.99% power to detect an average change of 0.5 medications between the control and intervention phase, assuming a SD of 1.5 medications, a 5% level of significance and an ICC of 0.05.

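### The main models for medicines stopped and for the proportion deprescribed omit the admission medicine count, which is already recorded and probably prognostic; adding it brings a modest gain

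*Protocol article*

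**What the plan says.** The Additional analyses section sets out two medication models. For the first, "The number of medications stopped during the enhanced data collection period will be compared between the control and intervention using a linear mixed model", with a random hospital effect and with arm and time period as the fixed terms named. For the second, "The proportion of patients per arm where a pre-admission medicine is proactively deprescribed will be compared using logistic regression, the same model as above". Neither names a patient-level covariate.

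The same section opens with the only planned covariate adjustment: "A sensitivity analysis will adjust for relevant baseline characteristics, that is, age and the number of pre-admission medicines". It does not say which outcome this serves. Coming straight after the primary analysis, it reads most naturally as referring to readmission.

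The Outcomes section shows that the covariate is available where these models need it. The outcome in Table 1 is "Number of medicines prescribed on admission which are stopped during admission while on study ward", and the table footnote on medication data lists "Name, dose and frequency of all medicines prescribed to the patient before any changes were made during the hospital admission" among the items collected.

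The Sample size section plans the enhanced periods on the condition "if the sites collect data on 60 participants in each of the enhanced data collection periods". It then claims "99.99% power to detect an average change of 0.5 medications between the control and intervention phase, assuming a SD of 1.5 medications", with "a 5% level of significance and an ICC of 0.05".

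**The concern.** The stopped medicines are a subset of the medicines on admission. A patient admitted on two cannot have four stopped, and a patient on none cannot have one deprescribed. The admission count is therefore likely to be related to both outcomes, and ward behaviour cannot affect it because it is taken before any change. The protocol itself treats it as relevant, but fixes its use only in a sensitivity analysis that probably concerns readmission, where the link to the outcome is less direct.

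Two things are at stake.

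- **Precision.** Variation in stops that the admission count explains stays in the residual.
- **Case mix.** Each hospital supplies one control month and one intervention month with different patients. The trial is unblinded, and data on those who decline are not collected. The random hospital effect handles stable differences between hospitals. It does not handle a change in who is sampled within a hospital from one month to the other.

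**Working it through.** **Inputs from the Sample size section:** difference 0.5, SD 1.5 (variance 2.25), ICC 0.05, 60 patients per hospital per enhanced period, 20 hospitals in four groups of five, 5% significance (taken as two-sided). Between-hospital variance is 0.05 × 2.25 = 0.1125 and patient-level variance is 0.95 × 2.25 = 2.1375.

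**Assumed, because the documents do not give it:** within-hospital correlation r between admission count and number stopped, 0.3 to 0.5. Patient-level variance is then multiplied by 1 − r², which is 0.91 or 0.75, a fall of 9% or 25%. The arithmetic covers the count only, not age.

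Throughout, power = Φ(0.5/SE − 1.96), with the SE from generalised least squares (random hospital, fixed period). As a check on the method, the primary outcome with 200 per hospital in each of five periods, variance 0.167 × 0.833 and difference 0.03 gives 89.54%, against the stated 89.5%.

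**Step 1. The stated 99.99%.**

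- 60 patients per hospital in each of six quarters, implementation quarter left out: SE 0.0896, Φ(5.58 − 1.96) = 99.985%.
- One control and one intervention sample per hospital, no period term: SE = √(2 × 2.1375/(60 × 20)) = 0.0597, power above 99.99%.

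The stated figure is reproduced. However, the first layout samples every control and active quarter and the second drops the period term, whereas the text describes two enhanced months per hospital and a model with a period term.

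**Step 2. Adjustment in those layouts.**

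| Layout | Unadjusted SE | r = 0.3 | r = 0.5 |
|---|---|---|---|
| Six quarters | 0.0896 | 0.0856 | 0.0779 |
| Before–after | 0.0597 | 0.0569 | 0.0517 |

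The SE falls by about 4% to 5% at r = 0.3 and 13% at r = 0.5. Power moves from 99.985% to 99.995% or more in the first layout and stays above 99.99% in the second.

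**Step 3. Two enhanced months per hospital with a period term.** Assume the control month is in the last control quarter and the intervention month in the first active quarter. Group g then has its control month in quarter g and its active month in quarter g + 2. Both conditions appear together only in quarter 3 (group 1 active, group 3 control) and quarter 4 (group 2 active, group 4 control). The arm effect is thus a comparison of 10 hospitals with 10 others:

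variance = (2/10) × [0.1125 + 2.1375(1 − r²)/60]

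- r = 0: 0.2 × (0.1125 + 0.0356) = 0.0296, SE 0.172, power 82.8%.
- r = 0.3: 0.2 × (0.1125 + 0.0324) = 0.0290, SE 0.170, power 83.6%.
- r = 0.5: 0.2 × (0.1125 + 0.0267) = 0.0278, SE 0.167, power 85.0%.

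The gain is small because 0.1125 of the 0.1481 in each hospital mean is between-hospital variance, which this calculation leaves unchanged. If the count also explained 25% of that part, the SE would be √(0.75 × 0.0296) = 0.149 and power 91.8%. That is a further assumption.

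**Step 4. Sensitivity to case mix.** Shift = slope × difference in mean admission count. With assumed slopes of 0.05 to 0.2 stops per admission medicine and assumed differences of 0.25 to 1 medicine, the shift is 0.05 × 0.25 = 0.0125 to 0.2 × 1 = 0.2 medicines, or 2.5% to 40% of the 0.5 target. The upper end is extreme as a chance event. With an assumed SD of 4 admission medicines and 1,200 patients per phase, the SE of a simple phase difference is 4 × √(2/1200) = 0.16, so one medicine is about six SEs.

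**The case against.** The strongest reply is that covariate lists for secondary outcomes belong in the SAP. The article's wording on fixed factors is open, and the Handling missing data section says that a fuller SAP will follow and take priority. This stands in part: nothing prevents the SAP from adding the covariate. But the article does more than stay silent. It writes out these two models and places this very covariate in a sensitivity analysis, so there is a stated choice to improve on.

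A second reply is that the adjustment is already planned and the fix only swaps main and sensitivity analyses. Since the sentence names no outcome, a reader cannot tell that it covers the medication outcomes at all.

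A third is that a linear covariate does not enforce the cap on the number stopped. That is true. The cap is a reason to expect the count to be prognostic, and no more is claimed.

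Two stronger readings are tempting, and the documents support neither.

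- **That the unadjusted effect is biased.** No imbalance in admission count is documented. Step timing is randomised, hospital and period are in the model, and chance imbalance is already reflected in the SE. Selection is possible in an unblinded trial, but Table 1's footnotes allow medication data to be collected under Section 251 approval where consent could not be sought, which narrows the room for it.
- **That the comparison has only 82.8% power, or gains nine points from adjustment.** The 82.8% depends on an assumed timing of the enhanced months, which Figure 1 may settle and which cannot be seen here. The nine points also require the count to remove a quarter of the between-hospital variance.

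**Conclusion.** The point holds as an inexpensive improvement, not as an error that invalidates the analysis. Both main medication models leave out a covariate that is recorded before any change, is held for the same patients and is very likely prognostic.

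The size is modest: a 9% to 25% fall in patient-level variance at r = 0.3 to 0.5. In the sparse two-month layout that is worth roughly one to two points of power; in layouts that match the stated 99.99% it is worth practically none. The correlation and the timing of the enhanced months are assumptions. Protection against a case-mix difference between two unblinded samples of different patients is the other benefit. Its size cannot be given from the documents.

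**What to change.** In Additional analyses, add admission medicine count and age as fixed covariates in the main linear mixed model for medicines stopped and in the main logistic model for the proportion proactively deprescribed. Report the models without them as the sensitivity analysis. Say which count is meant, for example regular plus as-required medicines, since Table 1 lists both on admission. Name the outcome that the existing sensitivity analysis serves.

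The cost is a sentence or two of text, with no new data or patients. There is one small downside: the odds ratio in the logistic model becomes conditional on the covariates and will not be directly comparable with the unadjusted one, so the plan should state this. The change should be made before any outcome data are seen, so that the adjustment does not look post hoc.

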#### Handling missing data

Due to the use of routinely collected data, it is unlikely that there will be significant missing data for the main analysis. If appropriate, we will use imputation to account for missing data for other non-routine outcomes.

A full SAP will be written prior to the start of any data analysis. As the SAP will be more detailed, any discrepancies in the analysis between the SAP and the protocol, the SAP will take priority.

### Health economics

A within-trial economic evaluation will be undertaken from the NHS perspective to estimate whether deprescribing is cost-effective.

Resources associated with providing the intervention will be included in the evaluation. This will include staff time required for activities such as attending workshops, watching video material, attending briefings, preparing an action plan and preparing benchmarking reports. The intervention may have an impact on resource use associated with NHS inpatient admissions in the follow-up period, as well as medicines use, which will also be investigated. For the consented sub-sample, data relating to Health Related Quality of Life and EuroQol 5-Dimension 5-Level (HRQoL (EQ-5D-5L)) and primary care contacts will also be collected.

Resource use data collection has been informed by lessons learnt from the feasibility study. The occurrence of activities related to the intervention, such as attendance at workshops, will be recorded by means of the fidelity framework conducted as part of the process evaluation. The protocol for the process evaluation will be reported separately.

The resource implications of these events will be costed by means of information obtained from the fidelity framework as well as additional insights gained from aspects of the feasibility study, for example, qualitative research. Where necessary, we will elicit further information required to cost the intervention. For example, eliciting expert opinion on the typical time required for deprescribing activities.

In terms of NHS resource use, data will be obtained from NHS England related to inpatient admissions and prescribing data. Additionally, data relating to the initial (recruitment) inpatient stay will be obtained from study sites. The feasibility study indicated that primary care-related resource use would be difficult to collect by the methods originally planned, namely either interviews with General Practitioners (GPs)/other primary care members with a prescribing role or general practice patient records review, without adding substantially to the burden of the study. For this reason, a bespoke section was added to the drug adverse event questionnaire to collect details of the participating patient’s participant primary care use at the 90-day follow-up telephone interview. The proposed questions have been shared with the trial management team and PPI members for comment. These data would be collected from the consented sub-study only. Resources identified will be combined with appropriate unit costs data, for example, NHS reference costs,^11^ to estimate the mean overall cost in each study arm. This will enable an estimate of any differences in the cost of the de-prescribing group compared with usual care.

The primary health economics analysis will be a cost-effectiveness study using the study’s primary outcome of re-admissions in the 90-day follow-up period. As part of the trial, we will collect measures of HRQoL using EQ-5D-5L.^23^ These will be collected in the consented sub-sample at baseline and at 90 days post-discharge, either by self-report or proxy response. This measure can be used to estimate quality adjusted life years (QALY), enabling the mean difference in QALY scores to be estimated (incremental effect). This will be carried out for the consented sub-sample and will be presented as a sensitivity analysis. As part of the analysis, we will explore whether it is sensible to use these values to impute QALY scores for the whole sample. If carried out, this will also be presented as an additional sensitivity analysis.

If the intervention arm is both less expensive, for example, due to lower medication or readmission costs, and more effective than usual care in terms of the primary outcome of readmissions at 90 days, then it would be said to dominate usual care and would be the preferred option. If neither the intervention nor the usual care is clearly preferred, we will estimate incremental cost-effectiveness ratios in terms of cost per re-admission prevented.^12^ The associated level of uncertainty will be characterised by estimating cost-effectiveness acceptability curves. Sensitivity analysis will also be undertaken to assess the robustness of results to changes in key assumptions. In line with the outcome analysis, all analyses will be conducted on an intention-to-treat basis. Appropriate actions will be taken where there is missing data, for example, imputing data by means of multiple imputation. As part of the health economic analysis, a health economics analysis plan will be written, in consultation with the CI and trial statistician and shared with team members.

A health economic model will be constructed to explore the effects of long-term changes in prescribing costs and mortality. The exact form of this model will be established in consultation with other members of the research team, as a clinical input to this process would be vital. A priori, this would be expected to take the form of a Markov model estimating cost per QALY.

### Data sharing

The protocol will be available on the NIHR website and within the ISRCTN register. The datasets generated during and/or analysed during the current study are not expected to be made available due to data sharing restrictions as part of section 251 approval and NHS England governance requirements. Statistical code will be available on request from [contact].

### Oversight and monitoring

NCTU is responsible for managing the trial including operational delivery, data management, statistical analysis, health economics and quality assurance.

The Trial Steering Committee responsible for overseeing the CHARMER research programme will take on the responsibilities of the Trial Steering Committee and Data Management Committee at the beginning of the trial. The committee consists of a research-active consultant geriatrician (Chair), national lead for provision of clinical pharmacy services, senior medical statistician, senior clinical trialist, senior behavioural scientist and two PPI members, who are all independent of the sponsor and have no competing interests. The Committee was convened to meet approximately 6 monthly at key timepoints. [name] (Co-CI and award holder) and [name] (Trial Statistician) are non-independent members. At least two representatives from NCTU, the funding award body, sponsor and trial team attend as observers reporting on progress and advising as requested.

As the primary outcome (readmissions to hospital) is obtained from routine data retained by NHS Digital and would not be available to the research team until after the last patient has completed, it was not possible to review the safety of the intervention during the trial.

### Adverse event reporting and harms

Adverse events are not being collected for this trial. Potential unintended harms arising from the intervention with respect to deprescribing discussions or the stopping or reducing of medications will be assessed by questionnaire in those participants who consent or for whom consultee assent is provided in the post-intervention enhanced data collection period. Harms identified will be reviewed by clinician members of the trial management group, categorised and reported as part of the trial publication. Complaints from participants, consultees, relatives or staff relating to the trial conduct will be directed to the Sponsor. NCTU will lead on investigating complaints in conjunction with the Trial Management Groups and Sponsor.

